## Abstract

**Background:**

The transition to adulthood is a unique developmental period characterized by numerous personal and social role changes and increased opportunities for alcohol consumption. Using alcohol to cope with anxiety symptoms is commonly reported, and young people with anxiety are at a greater risk of hazardous alcohol use and progression to alcohol use disorder. Anxiety and alcohol use tend to fuel each other in an exacerbating feed-forward cycle, leading to difficult-to-treat chronic problems. The peak in onset of anxiety and alcohol disorders suggests this developmental window represents a promising opportunity for early intervention before these problems become entrenched.

**Objective:**

This study aims to evaluate the efficacy of the *Inroads* program, a therapist-supported, internet-delivered early intervention for young adults that targets alcohol use, anxiety symptoms, and the interconnections between these problems.

**Methods:**

A randomized controlled trial will be conducted nationally among young Australians (aged 17-24 years) who experience anxiety symptoms and drink alcohol at hazardous or harmful levels. Participants will be individually randomized on a 1:1 basis to receive the *Inroads* intervention or assessment plus alcohol guidelines. Participants randomized to the *Inroads* intervention will receive access to 5 Web-based cognitive behavioral therapy (CBT) modules and weekly therapist support via email and/or phone. The primary outcome assessment will be 8 weeks post baseline, with follow-up assessment 6 months post baseline to determine the sustainability of the intervention effects. Primary outcomes will be the total number of standard drinks consumed in the past month (assessed by the Timeline Follow-Back procedure), severity of alcohol-related harms (assessed by the Brief Young Adult Alcohol Consequences Questionnaire), and anxiety symptoms across multiple disorders (assessed by the Generalized Anxiety Disorder-7). Secondary outcomes will include alcohol outcome expectancies; functional impairment and quality of life; and symptoms of social anxiety, anxious arousal, and depression. Results will be analyzed by intention-to-treat using multilevel mixed effects analysis for repeated measures.

**Results:**

The study is funded from 2017 to 2020 by Australian Rotary Health. Recruitment is expected to be complete by late-2018, with the 6-month follow-ups to be completed by mid-2019. Results are expected to be published in 2020.

**Conclusions:**

The study will be the first to evaluate the benefits of a youth-focused early intervention that simultaneously targets anxiety and hazardous alcohol use. By explicitly addressing the interconnections between anxiety and alcohol use and enhancing CBT coping skills, the *Inroads* program has the potential to interrupt the trajectory toward co-occurring anxiety and alcohol use disorders. The Web-based format of the program combined with minimal therapist support means that if effective, the program could be widely disseminated to reach young people who are not currently able or willing to access face-to-face treatment.

**Trial Registration:**

Australian New Zealand Clinical Trials Registry ACTRN12617001609347; https://www.anzctr.org.au/Trial/Registration/TrialReview.aspx?id=372748&isReview=true (Archived by WebCite at http://www.webcitation.org/77Au19jmf)

**International Registered Report Identifier (IRRID):**

DERR1-10.2196/12370

## Introduction

### Background

The transition from adolescence to early adulthood is a unique and important developmental period characterized by numerous personal and social role changes, including new relationships and living arrangements, increased independence, and pursuit of employment and/or higher education [1]. Young adulthood also marks a period of increased vulnerability for the onset of both anxiety and alcohol use disorders [2-5]. Up to 1 in 5 young people aged between 16 and 29 years report an anxiety disorder in the preceding 12 months (12.2%-22.3%) [6-9]. Experiencing anxiety symptoms at this important developmental stage affects the way a young person adjusts to changing life circumstances and can make it more difficult to form new friendships and navigate the challenges, increasing life demands and stressors that emerge [10]. Young adulthood is also characterized by increased availability and opportunities for alcohol use, coinciding with a change to the legal of drinking at age 18 years in many countries including Australia. Within a 12-month period, nearly 1 in 2 (42.0%) young adults aged 18 to 24 years report consuming alcohol at high-risk levels (ie, 5 or more standard drinks on a single occasion at least once a month) and approximately 1 in 6 (15.3%) at very high–risk levels (ie, 11 or more standard drinks on a single occasion at least once per year) [11]. Intoxication, particularly at this age, can have significant health, legal, social, and financial consequences, including progression to alcohol use disorder [1]. Patterns of alcohol use established at this age are linked to outcomes later in adulthood, including risk of chronic alcohol use problems and a range of physical, social, and mental health consequences [12]. Despite the profound potential impact, less than 1 in 4 young people with a mental health or substance use disorder will seek help for these problems [2,13]. For young people, common barriers to seeking treatment include fear of judgment or stigma and practical constraints including difficulty accessing treatment at a convenient time or location [14].

### Interrelationship Between Anxiety and Alcohol Use

Anxiety has been consistently associated with increased risk of hazardous alcohol use and alcohol use disorder [15,16]. In view of evidence that the onset of anxiety symptoms typically precedes that of hazardous alcohol use [15], the co-occurrence of anxiety and alcohol use is often explained by the self-medication model [17,18], whereby alcohol is consumed in an attempt to reduce or cope with anxiety symptoms. Over time, this can lead to progressively greater alcohol intake, related psychosocial problems, functional impairment, and heightened stress and anxiety [19,20]. Among young people, overly positive expectancies about the tension-reducing and social lubricant effects of alcohol are common, and anxious young people may be particularly susceptible to the use of alcohol to cope with symptoms of anxiety and nervousness as they navigate new social and occupational challenges [21,22]. Indeed, coping-motivated drinking has been linked to the development of alcohol-related problems [23-25], and anxiety disorders are associated with an earlier first use of alcohol [26] and increased risk of progression from first alcohol use to regular use and from regular use to alcohol use disorder [27]. If left untreated, anxiety and hazardous alcohol use tend to fuel each other in an exacerbating feed-forward cycle that interferes with recovery from either condition [28-31].

### Integrating Anxiety and Alcohol Use Interventions Improves Outcomes

People with co-occurring anxiety and hazardous alcohol use tend to respond poorly to standard, single-disorder interventions [32-34]. Increasingly, the co-occurrence of anxiety symptoms and hazardous alcohol use is understood as a clinically important relationship involving mutually reinforcing connections that are likely to require integrated interventions [16,35]. Evidence from adult samples [30,36,37] suggests integrating treatment for co-occurring anxiety and alcohol use disorders is a promising approach that is intuitively appealing to patients. Our research group has developed an integrated cognitive behavioral therapy (CBT) for co-occurring social anxiety and alcohol use disorders [28], which has demonstrated greater improvements in anxiety symptoms, depression, and overall functioning compared with standard treatment approaches [37]. Furthermore, our work with young adolescents (aged 13-14 years) has demonstrated that early intervention implemented in secondary schools to improve coping with high-risk personality traits, including anxiety sensitivity, effectively reduces alcohol misuse and alcohol-related harms over a 3-year period [38]. Most recently, a randomized controlled trial (RCT) of a youth-focused, internet-delivered, early intervention targeting co-occurring depression and harmful alcohol use has demonstrated clinically significant short-term symptom improvements compared with an attention control among young adults [39]. These findings demonstrate the clear clinical benefits of integrated approaches and demonstrate that age-appropriate early intervention has the potential to prevent or halt the escalation of anxiety and drinking into disorder-level problems.

### The Inroads Program: Providing Accessible, Age-Appropriate, Early Intervention for Young Adults

The increased availability and opportunities for drinking during early adulthood, combined with the peak in onset of anxiety disorders, suggests this is a critical developmental window for interrupting the trajectory into chronic anxiety and alcohol use disorders. Despite the associative links between anxiety and hazardous alcohol use, there are no existing youth-focused interventions that target anxiety symptoms, hazardous alcohol use, and the interconnections between them. The internet presents a promising delivery method for this age group as it reduces barriers to seeking treatment such as fear of judgment or stigma, cost, and difficulties accessing treatment [14]. Reviews suggest young people prefer internet-delivered over face-to-face treatments [40], and limitations relating to engagement and retention can be ameliorated through the provision of therapist support via phone, chat, or email [41]. To meet this need for an age-appropriate, internet-delivered, integrated intervention targeting anxiety and hazardous alcohol use, the *Inroads* program was developed. The program was designed in consultation with the target age group to ensure the content and features (ie, case vignettes, skill-based videos, language, illustrations, and layout) were deemed relevant, acceptable, and appealing and would maximize engagement of anxious young people at risk of hazardous alcohol use. This brief, 5-session intervention combines therapist phone and email support with internet-delivered CBT content via contemporary Web design, youth-focused illustrations, videos, and vignettes. The active intervention components draw from our integrated CBT program for adults with social anxiety and alcohol use disorder [28] and our Web-based youth program for alcohol use and depression treatment [39]. The *Inroads* program and development process are described in full elsewhere [42].

### Aims

This study will evaluate the efficacy of the *Inroads* program—a brief, Web-based CBT intervention that combines 5 online skills-based modules with minimal psychologist support for young adults (aged 17-24 years) who experience both anxiety symptoms and hazardous or harmful alcohol use. The study will be an RCT comparing the *Inroads* program with a control condition who will receive assessment plus alcohol guidelines and information. The study will be the first to evaluate the benefits of an early intervention for young adults targeting hazardous alcohol use, anxiety symptoms, and the interconnections between these problems.

It is hypothesized that compared with the control condition, the *Inroads* intervention will achieve greater reductions in (1) alcohol use, including drinks per drinking day and frequency of binge drinking; (2) alcohol-related harms; and (3) anxiety symptoms at 8 weeks post baseline. To assess the sustainability of these effects, outcomes for both groups will be assessed again at 6 months post baseline. Furthermore, it is hypothesized that participants allocated to receive the *Inroads* program will report decreased coping-motivated drinking and positive alcohol expectancies and greater improvements from baseline to post intervention on secondary outcomes of stress, social anxiety and depression symptoms, overall functioning, and quality of life.

## Methods

### Study Setting and Design

The study will be conducted nationally across Australia and involves a parallel RCT in which eligible participants will be individually randomized into either (1) the intervention condition (*Inroads* program) or (2) the control condition (assessment plus alcohol guidelines and information). The primary end point will be the posttreatment assessment, conducted at 8 weeks following baseline, with a secondary end point at 6 months after baseline. Figure 1 depicts the study design.

### Ethics Approval and Registration

The study has been prospectively registered with the Australian New Zealand Clinical Trials Registry (ACTRN12617001609347) and received ethical approval from the University of New South Wales Human Research Ethics Committee (HC17185). Informed consent will be obtained electronically from all participants and confidentially assured via rigorous data encryption.

### Participants

A total of 122 participants (male and female) aged between 17 and 24 years who report anxiety symptoms and hazardous or harmful alcohol consumption will be recruited into the study in 2018. This age range captures the transition from late adolescence at 17 years into the unique developmental stage of young adulthood [43].

#### Recruitment

Participants will be recruited through a variety of advertising methods including media coverage (TV and radio), social media posts, paid online advertising via social media and search engines (eg, Facebook, Twitter, Instagram, YouTube, and Google search), distribution of posters and flyers at universities, technical and further education institutes and youth-focused institutions, and referral from youth mental health services. Potential participants will be referred to the study website [44], which provides a description of the study. To be assessed for the study, interested participants will click a link to provide informed consent before proceeding to the online eligibility assessment.

### Eligibility Criteria

Individuals who consent to participate will be directed to complete a 15-min online eligibility assessment. Inclusion and exclusion criteria are shown in Textboxes 1 and 2, respectively. Eligible participants will be invited to complete an online baseline assessment before proceeding with the trial. Participants who do not meet eligibility criteria will be provided with a list of referral options.

**Figure 1 figure1:**
[figure not shown]
Inroads study design. CBT: cognitive behavioral therapy.

Inclusion criteria.Aged between 17 and 24 years.Living in Australia.Currently reporting hazardous or harmful levels of alcohol use, as indicated by an Alcohol Use Disorders Identification Test score ≥8 [45].Experiencing at least mild symptoms of an anxiety disorder, as indicated by a score ≥5 on the Generalized Anxiety Disorder-7 (GAD-7) Questionnaire [46] or a score ≥6 on the Mini-Social Phobia Inventory (Mini-SPIN) [47]. Although the Mini-SPIN focusses on anxiety symptoms consistent with social anxiety disorder, the GAD-7 has been found to index symptoms across multiple disorders and is sensitive to GAD, panic, and social anxiety disorder, facilitating screening of young people presenting with a range of anxiety presentations [48].

Exclusion criteria.Inability or unwillingness to provide contact information.Insufficient English literacy.Inability to access the internet to participate in the program.Daily use of cannabis or benzodiazepines or weekly use of psychostimulants (assessed by the National Institute on Drug Abuse quick screen questions [49]).Primary current concern as identified by the participant is related to trauma symptoms or substance use other than alcohol.Significant risk of complicated alcohol withdrawal (indicated by past experience of severe alcohol withdrawal symptoms such as seizures, hallucinations, or high fever).Active suicidal ideation (indicated by a single item assessing experience of suicidal thoughts and intent in the past 2 weeks).Active symptoms of psychosis (score ≥3 on the Psychosis Screening Questionnaire [50]) or currently accessing ongoing psychological treatment for mental health or drug or alcohol problems.

### Allocation

To avoid bias, participants will be individually randomized to either the intervention or control condition via the trial website using a computer-generated randomization sequence, which is concealed from the investigators. Automatic randomization within the Web-based program removes the potential for researcher involvement. Randomization will occur directly after completion of the online baseline assessment. Following randomization, the study psychologists ([name]) and project coordinator (KP) will be informed of group allocation to deliver the intervention (phone or chat sessions and motivational emails) to participants allocated to the intervention condition, whereas the research assistant (BL) who is responsible for reminding participants to complete follow-up assessments will remain blind to allocation status.

### Assessments

All assessments are well-validated instruments commonly used in mental health and alcohol research and will be administered online via the trial website hosted by a secure, dedicated server in Australia. Participants will complete an online eligibility screening and baseline assessment before random allocation. Automatic email prompts to complete follow-up assessments will be sent to participants at 8 weeks (primary end point) and 6 months (secondary end point) after baseline. The following evidence-based strategies will minimize data attrition [51,52]: (1) monetary incentives (Aus $30 gift voucher) for each follow-up assessment completed, (2) collection of multiple sources of contact information at baseline (eg, email, mobile number, and postal address), (3) user-friendly electronic survey design that can be completed via multiple devices (eg, via mobile phone), (4) personalized reminder messages (short message service [SMS] text message and email) to complete survey, and (5) follow-up letter with photo of the research team and telephone call from the research assistant (blind to allocation status) to those participants who do not respond. Self-report assessment, use of standardized reminder templates, and blinding of the research assistants administering follow-up calls removes the potential for researcher influence over study results. The timing of assessments is detailed in the *Inroads* study schedule in Table 1.

### Measures

Primary and secondary outcomes of the study were assessed at baseline, 8-weeks post baseline, and 6-months post baseline using validated psychometric instruments.

#### Primary Outcomes

Due to the focus of the study on co-occurring anxiety and hazardous alcohol use, primary outcomes encompass measurement across both anxiety symptoms and alcohol-related problems. Primary outcomes for alcohol are consumption per drinking day, calculated from the total number of Australian standard drinks (10 g of alcohol) consumed in the past month and assessed by a computerized version of the Timeline Follow-Back (TLFB; [53,54]) procedure and alcohol-related harm as assessed by the Brief-Young Adult Alcohol Consequences Questionnaire (B-YAACQ; [55]). The TLFB is a widely used procedure that has been validated across a number of countries and among a variety of subpopulations, including young adults, and the self-report computerized version has demonstrated good reliability with test-retest correlations exceeding 0.85 (see review by Deady [56]). The B-YAACQ assesses 24 age-appropriate consequences of alcohol consumption in the past 30 days using a dichotomous (0 “no” or 1 “yes”) response format. Scores range from 0 to 24, with higher scores indicating more problems and negative consequences from drinking. Primary outcomes for anxiety will be assessed by the Generalized Anxiety Disorder-7 (GAD-7) [48], which is sensitive to symptoms across anxiety disorders and has been previously used to assess outcomes in trials of internet-delivered treatment for mixed anxiety samples [57]. The GAD-7 contains 7 items, ranging from 0 “not at all” to 3 “nearly every day.” Total scores range from 0 to 21, with scores of 5, 10, and 15 representing cut points for mild, moderate, and severe anxiety, respectively.

**Table 1 table1:** *Inroads* study timeline.

Assessments		Study period				
		Enrollment	Pre-allocation	Allocation	Post-allocation	
			t_1_ (baseline)		t_2_ (8 weeks)	t_3_ (6 months)

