### Sample Size

Previous evaluations of brief, multisession, internet-delivered interventions for young adults have indicated an effect size at post intervention of between 0.68 and 0.99 for reduction in the number of drinks consumed [39,75], 0.56 for reduction in alcohol-related consequences [75], and 0.59 for reduction in anxiety symptoms [76]. Optimal Design software [77] was used to calculate the required sample size, taking into account the multilevel analysis with a nested repeated measures design. Using a conservative approach with intraclass correlation coefficient of .55 estimated based on our adult comorbidity trial [37], power calculations indicated a sample size of 90 (45 each group) would be required to detect a moderate effect size of 0.50 between the intervention and control group with power=0.8 and alpha=.05. To allow for data attrition at post assessment, estimated at 35% (n=32/90) [78], a total sample of 122 individuals will be recruited to the study.

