### Statistical Analysis

Primary analyses will use multilevel mixed effects analysis for repeated measures [79,80], which is a flexible analytic approach for modeling change over time that has emerged as a flexible and rigorous method for analyzing RCT results. The approach has a number of advantages over traditional approaches, including better treatment of missing data and flexible modeling of variance at the individual level, time effects, and the within-subject covariance structure [79,80]. Models will include a random intercept, and preliminary models will be estimated and model fit statistics examined to determine the most appropriate model and covariance structure. All models will use baseline measurements as the reference point to estimate participant-specific starting points and change over time. Intervention condition will be represented by a dummy-coded variable, and the condition by time interaction will be examined to assess between-group differences in treatment response over time. Treatment dose (hours of therapist contact and module completion) will be entered as an independent variable in secondary analyses to examine moderation of treatment effects. For outcomes with evidence of significant intervention effects, Cohen *d* will be calculated from model estimated marginal means and standard errors to determine the size of effect between conditions at the relevant end point. All analyses will be carried out on an intention-to-treat basis, retaining and analyzing all participants in the intervention groups they were originally allocated to. Missing data will be accounted for in all analyses using maximum likelihood estimation, and the impact of missing data on study conclusions will be examined using recommended methods [81]. Data analyses will be conducted using Stata, version 15 [82], with significance levels set at *P*<.05 (95% CI).

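### Three primary outcomes are each tested at P<.05 with no rule for judging success across them, so neither 5% error nor 80% power is secured for an overall efficacy conclusion

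*Protocol article*

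**What the plan says.** Under Primary Outcomes the protocol article explains that "primary outcomes encompass measurement across both anxiety symptoms and alcohol-related problems". Three are then named:

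- drinking: "Primary outcomes for alcohol are consumption per drinking day, calculated from the total number of Australian standard drinks" (by TLFB);
- harms: "alcohol-related harm as assessed by the Brief-Young Adult Alcohol Consequences Questionnaire";
- anxiety: "Primary outcomes for anxiety will be assessed by the Generalized Anxiety Disorder-7 (GAD-7").

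Study Setting and Design makes the 8-week assessment the primary end point and 6 months the secondary one. The Aims section lists alcohol use, harms and anxiety as three numbered predictions.

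Statistical Analysis gives a single significance criterion, "with significance levels set at *P*<.05 (95% CI"), and provides for an effect size to be reported for each outcome that shows a significant effect. Sample Size is based on an "effect size of 0.50 between the intervention and control group with power=0.8 and alpha=.05". No section orders the three outcomes, divides alpha, adjusts the tests, or says how many must be significant for the program to be judged efficacious.

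**The concern.** The trial asks one program-level question, whether Inroads is efficacious, and has three primary tests that could each answer it. The 5% and 80% that the article quotes are properties of one test. They carry over to the program-level conclusion only under a decision rule, and none is given.

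If one significant outcome out of three is enough, the chance of a false positive conclusion exceeds 5%. If all three are needed, the chance of success is below 80% at the planned effect. A rule chosen after the results are seen could favour whichever reading suits them.

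**Working it through.** **Inputs from the article.** Three primary outcomes (Primary Outcomes). Alpha 0.05 per test, taken as two-sided because 95% intervals are quoted (Statistical Analysis). d = 0.50, power 0.80, intraclass correlation 0.55, 45 per arm (Sample Size). Three assessments: baseline, 8 weeks, 6 months (Measures).

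**Assumption.** The article gives no correlation between the three test statistics. A common correlation from 0 to 0.7 is used below.

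**Step 1: reproduce the planned sample size.** Averaging three measures with intraclass correlation 0.55 gives a variance factor of (1 + 2 × 0.55)/3 = 0.70. A two-sample comparison with d = 0.50, that variance and two-sided alpha 0.05 needs 45 per arm by the noncentral t distribution (power 0.801), or 44 by the normal approximation. The stated 45 per arm is therefore reproduced with the whole of alpha spent on one comparison; no multiplicity allowance is built in.

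**Step 2: error if any one significant outcome suffices.** For independent tests the family-wise error is 1 − 0.95³ = 0.1426. The bound under any dependence is 3 × 0.05 = 0.15. For correlated tests, three two-sided z tests were simulated with no true effects.

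**Step 3: power if all three must be significant.** Each test has marginal power 0.80, that is, d = 0.50 on every outcome. For independent tests joint power is 0.80³ = 0.512. Correlated cases were simulated.

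| Assumed correlation | Family-wise error, any of three | Joint power, all three |
|---|---|---|
| 0 | 14.3% | 0.51 |
| 0.3 | 13.6% | 0.57 |
| 0.5 | 12.5% | 0.61 |
| 0.7 | 10.9% | 0.66 |

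**Step 4: power under Holm, from 0.80 marginal power.**

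- All three effects real at 0.50: simulated per-outcome power is 0.75 (correlation 0), 0.74 (0.3), 0.74 (0.5) and 0.73 (0.7). The chance of at least one claim runs from 0.96 down to 0.83 over the same range.
- Only one effect real: that outcome usually has to pass Holm's first step at 0.05/3 = 0.0167. With critical values 1.960 and 2.394, power there is Φ(0.842 + 1.960 − 2.394) = Φ(0.408) = 0.66. Simulation of the full procedure also gives 0.66 at every correlation tried.

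**The case against.** **The handling of alpha may sit in an analysis plan that is not shown.** The mechanics of an adjustment can properly be left there, and the P<.05 sentence does not say that the tests are unadjusted; Holm at an overall 0.05 could be read into it. That is fair. But the article itself fixes one criterion, judges outcomes one at a time and spends the full alpha in the sample size. An adjustment elsewhere would still leave the stated power wrong for the adjusted tests.

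**A reader might infer that the plan declares success on any single significant outcome, and so has a 14% error rate as written.** The documents do not support that. No such rule is stated, and the Aims join the three predictions without saying how many must hold. If each claim is confined to its own outcome, each keeps its 5% error, and whether family-wise control is then needed is debated. In addition, 14.3% is the independence case. Drinking and its consequences are unlikely to be independent, so the lower part of the range may be nearer the truth.

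**The all-must-succeed figure depends on d = 0.50 for every outcome.** Sample Size cites larger effects: 0.68 to 0.99 for drinks, 0.56 for harms, 0.59 for anxiety. Scaling the stated power to 0.68, 0.56 and 0.59 gives marginal power of about 0.97, 0.88 and 0.91, and joint power of about 0.78 (independent) to 0.81 (correlation 0.5). The shortfall is therefore a statement about the planning effect, not about the effects cited. This stands as a limit on the size, but 0.50 is the effect at which the article claims 80%.

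**The 6-month tests are not part of this problem.** The article already makes 6 months the secondary end point.

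**Conclusion.** The point holds as a conditional one. Three primary tests, each at P<.05 and each planned at full alpha, come with no rule that combines them. On an any-one reading the family-wise error is about 11% to 14% (at most 15%) instead of 5%. On an all-three reading the joint power is about 0.51 to 0.66 instead of 0.80.

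Both ranges rest on assumed common correlations between 0 and 0.7, and the second also on a true effect of exactly 0.50 on each outcome. The article does not say which reading applies. The trial remains sound, but the rule should be fixed before the outcome data are analysed by arm.

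The count of three also presumes a single drinking measure. The abstract's Methods paragraph says "Primary outcomes will be the total number of standard drinks consumed in the past month", whereas Primary Outcomes uses consumption per drinking day. One of them has to be chosen for the family of tests to be defined.

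**What to change.** State in Statistical Analysis, and carry into the analysis plan, that the three primary outcomes at 8 weeks are tested by Holm's step-down procedure at an overall two-sided 0.05, and that efficacy is claimed only for the outcomes that pass. Restate the power in Sample Size per outcome under Holm.

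Holm holds the family-wise error at or below 5% under any dependence. The cost is wording plus some power. From 0.80 marginal power, per-outcome power becomes about 0.73 to 0.75 if all three effects are real and about 0.66 if only one is. The second figure should be reported alongside the first. No increase in sample size is asked for.

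An acceptable alternative is an explicit rule that all three outcomes must be significant at 0.05, with joint power given in place of 0.80 and the assumed correlation stated.
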